# Self-Monitoring by Traffic Light Color Coding Versus Usual Care on Outcomes of Patients With Heart Failure Reduced Ejection Fraction: Protocol for a Randomized Controlled Trial

**DOI:** 10.2196/resprot.9209

**Published:** 2018-11-14

**Keywords:** heart failure, outcome, self-monitoring, clinical trial

## Abstract

**Background:**

Patients with heart failure (HF) reduced ejection fraction (HFrEF) have symptoms that are more severe and experience a higher rate of hospitalization compared with HF preserved ejection fraction (HFpEF) patients. However, symptom recognition cannot be made by patients based on current approaches. This problem is a barrier to effective self-care that needs to be improved by new self-monitoring instruments and strategies.

**Objective:**

This study describes a protocol for the self-monitoring daily diaries of weight and shortness of breath (SOB) based on the traffic light system (TLS). The primary objective is to compare the self-care between the intervention and control group. Comparison of HF knowledge, HF quality of life (HFQOL), and all-cause hospitalization between the 2 groups are the secondary objectives.

**Methods:**

A single-blind randomized controlled trial is being conducted at the HF clinic at Tehran Heart Center (Tehran, Iran). Sixty-eight adult patients of both genders will be enrolled during admission to HF clinic. Eligible subjects will be assigned to either the intervention or control group by a block balanced randomization method. Baseline surveys will be conducted before random allocation. Participants in the intervention group will receive an integrated package consisting of (1) HF self-care education by an Australian Heart Foundation booklet on HF, (2) regular home self-monitoring of weight and SOB, and (3) scheduled call follow-ups for 3 months. Patients in the control group will receive no intervention and they only complete monthly surveys.

**Results:**

This study is ongoing and is expected to be completed by the end of 2018.

**Conclusions:**

This is the first trial with new self-monitoring instruments in Iran as a low and middle-income country. If the findings show a positive effect, the package will be applied in different regions with the same health care status.

**Trial Registration:**

Iranian Registry of Clinical Trials IRCT2017021032476N1; https://en.irct.ir/trial/25296?revision=25296 (Archived by WebCite at http://www.webcitation.org/73DLICQL8)

**International Registered Report Identifier (IRRID):**

PRR1-10.2196/9209

## Introduction

Heart failure (HF) is a complex clinical syndrome that results from any structural and functional impairment of ventricular filling or ejection of blood. Based on left ventricle dysfunction and the left ventricle ejection fraction (LVEF), HF can be categorized as preserved ejection fraction (with LVEF≥50%, known as HFpEF or diastolic HF) and reduced ejection fraction (with LVEF ≤40%, known as HFrEF or systolic HF) [1].

As a global burden, HF affects more than 37.7 million individuals worldwide [2] and is a common condition with 1%-2% total health resources allocated in high-income countries. In low- and middle-income countries (LMICs) like Iran, HF may displace infectious diseases as the major public health issue [3]. In Iran and other Asian LMICs, HF is described as a pandemic [4], the prevalence greatly increased with age and range between 0.5% to 9.0% among different cities, regardless of time distribution [5], thus supporting the need for better HF surveillance and management strategies [3]. Patients with HF can experience various clinical outcomes including mortality, morbidity, and other patient-reported outcomes [6]. Although mortality and morbidity rates are similar for HFpEF and HFrEF, the hospital admission rates in patients with HFrEF are much higher than HFpEF [7].

HF is a leading cause of hospitalizations [8], mortality [8,9], rising health care costs (over US $39 billion annually in the United States and US $53.1 billion by 2030) [2,8-10], suboptimal self-care behavior [11], and reduced quality of life (QOL) [12]. According to a recent European Society of Cardiology Heart Failure Long-Term Registry prospective observational study, the rate of all-cause mortality and hospitalization at one-year follow-up was 8.1% and 28.2%, respectively [13]. Compared to Western countries, patients with HF in Asia and Iran are younger, have more severe signs and symptoms, and receive lower levels of treatment compared to the European Society of Cardiology and American College of Cardiology Foundation/American Heart Association Guidelines [14]. Moreover, Callender et al [3] reported that Iranian patients with HF experience significantly lower rates of admission (0.3%).

Poor self-care and low QOL among patients with HF are major global health issues [11] that are also affecting Iran [15-17]. Adequate self-care is associated with an improved health status [18], fewer symptoms, higher QOL [19], and reduced hospitalizations [18]. A lack of knowledge of symptom recognition and psychological problems have been identified as 2 key barriers [20]. Therefore, effective educational methods are essential for improved self-care [11,20]. Previous studies have shown that self-care programs for patients with HF are most effective when specialized education is combined with symptom monitoring and response management [21,22]. Practical and user-friendly self-monitoring tools can help patients recognize, monitor, report, and manage the symptoms appropriately. Without these tools, HF decompensation may not be detected in the early stages and could lead to preventable hospitalizations [23].

Patients with HF experience weight gain and other serious decompensation symptoms including shortness of breath (SOB) due to pulmonary edema, fatigue, and leg swelling [24-26]. Weight gain resulting from fluid retention is a marker of HF decompensation, and therefore, frequent weight monitoring can identify high-risk periods in the early stages to prevent hospitalization [24]. However, low compliance with weighing has been reported among patients with HF [27].

Diaries in a textual/tabular format are acceptable and creative self-monitoring tools because they reinforce patient education and facilitate their disease management [28]. Improved HF clinical and hospital outcomes have been reported by weight and symptom self-monitoring diary users [29]. However, despite the lower rate of HF-related hospitalizations [21,30], reduced mortality rate [21], and improved self-care [22], the previously reported studies used tabular format diaries and were conducted in developed countries with a higher quality of health care. The results may not apply to developing countries with significantly different health care systems and levels of health care quality.

Graph format diaries have been reported to attract and hold a person’s attention for more extended periods and are the preferred format due to improved patient comprehension and information extraction [31]. Recently, a traffic light system (TLS) of diaries in graphical format have been developed [32]. The system consists of 3 different color codes: (1) red for medical alert, (2) yellow for a situation that is worsening and requires the patient to take quick-relief medications, and (3) green to show that the patient is doing well and adequately adhering to the treatment plan [33]. The TLS has been shown to be more effective in transforming information on risk assessment and disease management [32].

Wakefield et al [23] employed a pretest-posttest longitudinal design study to assess weight, and SOB self-monitoring by graphical instrumentation (other than TLS) in patients with HF. The paper revealed that self-monitoring HF patients could not complete the appropriate actions for each zone. Consequently, new strategies and instruments to actively engage patients in symptom recognition and monitoring require further research [23].

This study will combine graphical and tabular formats with TLS color coding to design weight and SOB self-monitoring diaries. Each color zone has been designed for patients to perform specified actions following symptom monitoring. The efficacy of this intervention will be compared with the usual care for patients with HF. This is the first practical study with new user-friendly self-monitoring tools that will be conducted in Iran as an LMIC to compare the primary outcome of self-care behavior and the secondary outcomes of HF-knowledge, QOL, and all-cause hospitalization between intervention and control groups.

## Methods

### Study Design

This study is a parallel, single-blind, randomized controlled trial. The study protocol has been reviewed and approved (No. 9411449005) by the Institutional Review Board (IRB) at Tehran University of Medical Sciences (TUMS, Tehran, Iran). The study protocol is based on the Standard Protocol Items: Recommendations for Interventional Trials (SPIRIT) 2013 guideline [34].

### Study Setting

This study will be conducted at the Tehran Heart Center (THC) HF clinic affiliated with TUMS. THC is one of the best equipped diagnostic and therapeutic cardiology centers with full-time specialists and well-trained nursing staff in the region and is a referral center for cardiology in Iran with more than 1,300,000 outpatient visits, and 280,000 patient hospitalizations from 2001 to the end of 2017 [35].

### Eligibility Criteria

The research nurse (author MN) will screen the medical records of adult patients (≥18 years of age) of both genders for the following inclusion criteria in the HF clinic. The eligibility of each participant will be confirmed by the HF specialist (see Textbox 1).

### Intervention

In this study, the intervention is an integrated package consisting of 3 components: (1) HF self-care education, (2) regular home self-monitoring of weight and SOB, and (3) scheduled call follow-ups.

The first component of the package includes HF self-care education that will be delivered in the HF clinic of the THC according to the Australian Heart Foundation educational booklet entitled “living well with chronic HF” [38]. Individual education will be provided by the research nurse (MN) according to the participants understanding and literacy for a 40-minute face-to-face session between 8 am to 1 pm. A Farsi version of the booklet will be given to each participant. Also, during the educational session, the instructor and the participant will review the booklet content together, and the instructor will answer any questions. The booklet contains information on disease definition, diagnosis, symptoms, and ways to manage them, lifestyle issues, medicines, and other treatments. In order to obtain permission to translate the booklet to Farsi language for local use in Iran, one of the authors (MN) contacted the Australian Heart Foundation on April 5, 2016. After obtaining permission, it was translated to the Farsi language by an individual who was also proficient in the English language and knowledge of cardiovascular terminologies. Two nursing faculty members and 2 cardiology faculty members affiliated with TUMS approved the Farsi version of the booklet.

Participant eligibility criteria.
**Inclusion criteria**
Definitive diagnosis of heart failure by an heart failure specialist documented on the clinical recordHeart failure reduced ejection fraction where ejection fraction ≤40% [36,1] by any method (transthoracic, or transesophageal echocardiography, and angiography)New York Heart Association function class II-IVAccess to a telephone, telegram mobile application, and ability to answer phone callsAbility to read and write in the Farsi languageHaving a functional weighing scale (digital or analog) at home to weigh daily [23]The absence of diagnosed hearing loss and sight defectsA stable hemodynamic statusNon-smoking, no drinking alcohol, and no addiction to drugsLiving at home and not in a homeless shelter [37]
**Exclusion criteria**
Diagnosed psychiatric and cognitive conditions during the studySudden death, migration, or unavailability of patients during the follow-up phaseRecording weight and shortness of breath in the daily diary for less than 60% (<54 days) during the studyUndergoing cardiac or other kinds of surgery with a lengthy hospital stay during the studyAwaiting or receiving a transplanted heart or a left ventricular assistive device

The second component of the package includes regular home self-monitoring of weight and SOB and recording them in the appropriate 3-color daily diaries for 3 months. Since the graphical display of values help patients to recognize their symptoms and contact their health care provider [23], we created a paper-based weight and SOB self-monitoring daily diary color-coded system that was analogous to TLS.

Based on previous studies, a graphical representation of health-related information is the preferred method for patients compared to numerical/tabular displays [39,40] for communicating medical risk information [41]. This approach results in better participant comprehension. The patient pays attention and extracts more information with less effort [31]. Thus, both research diaries have been designed in 3 colors and categorize the participants’ condition into 3 color-coded zones: green (excellent), yellow (use caution), and red (warning). The green, yellow, and red color-coded zones have been defined based on a combination of American Heart Association self-check plan for HF management [42] and the HF self-monitoring toolkit [43]. The colored diary will display recorded data in both graphical and tabular format. It is expected that this will result in a better participant understanding of their condition.

In the HF clinic, participants will be instructed by the research nurse on the daily measurement of weight and SOB and recording them in the daily diary during a 20-minute individual session between 8 am and 1 pm. The weight diary is a 7-page colored diary with instruction on the first page followed by 6 blank pages to record daily weight for 15 continuous days on each page.

At the time of referral to the THC, the HF specialist will measure the weight of eligible participants by analog weight scale (RASA scale, model 230, Iran). Then, 2 upper control limits will be determined for participants by the research nurse to identify 1 and 2.5 kg greater than the baseline weight that is considered as yellow and red zones in the weight diary, respectively [23] (see Figure 1). During instruction, the participants will be asked to weigh themselves daily after going to the toilet, before breakfast, with the same type of clothing, at the same time [38] and record it regularly in the weight diary for 3 months. If participants miss a weight measurement for any reason, they will be asked to record the reason for the missed date. They also will be instructed to contact the research nurse in case of sudden weight gain of 1 kg in one day (yellow zone) and 2.5 kg in one week (red zone) [44].

The SOB diary is a 4-page colored diary that includes instructions on the first page and 3 blank pages to record the difficulty of breathing for 30 continuous days on each page. The participants will be instructed on how to use the SOB colored diary, and how to rate the difficulty of breathing for the entire day after taking evening medications and at the end of each day for 3 months [23]. They will also be instructed to record the reason for any missed measuring dates.

The SOB rating scale was designed based on 0 to 10 pain assessment visual analog scale. In this scale, scores are categorized as follows: none (0), mild (1-3), moderate (4-6), and severe (7-10) [45] that have been marked by green, yellow, and red colors, respectively. Green, yellow, and red color zones will be explained to participants as no new or worsening (none-mild SOB), worsening with activity or at night when lying down (moderate SOB), and struggling to breath or at rest or while sitting (severe SOB), respectively [42] (see Figure 2). Participants will be instructed to contact the research nurse if they reach the yellow color zone to increase the diuretic dosage and contact with the emergency medical services in the red color zone [38].

The third component of the package includes scheduled follow-up phone calls (days 1, 3, and 7 after referral to the HF clinic and every week after that) for 3 months [21]. The research nurse will give participants a list of call dates and will call each subject in the evenings between 6 pm and 9 pm. Each follow-up phone call will last 5-15 minutes [21] and is designed to review the content of the instructional session, encourage participants to continue weight and SOB self-monitoring, and record them in the daily diaries. Also, the research nurse will ask the participants about the color zone during the previous week and will recommend the appropriate action (see Figure 3). Also, we predict that during the call follow-ups, participants in the intervention group will report another symptom that may be due to a side effect of the medications or the disease. The research nurse will be able to provide the appropriate recommendation for each symptom reported in the intervention group during these (see Figure 4).

At the end of the one-hour instructional session in the HF clinic, a plastic folder containing the instructional booklet, weight, and SOB colored diaries, pen, pencil, eraser, and a pencil sharpener will be delivered to each subject in the intervention group. They will be asked to keep diaries clean and deliver them to the research nurse at the end of the study.

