### Control

After randomization and allocating participants to 2 groups, those in the control group will receive the usual care. In HF clinic at THC, usual care for patients with HF is limited to a brief instruction by HF specialists on limiting water and salt intake, taking medications as prescribed, physical activity, weight monitoring and increasing the diuretic dosage in the condition of peripheral edema, weight gain, and SOB. They will receive 1 monthly phone call for 3 months. Out of respect for the ethical principles of human research, HF self-care instruction will be provided to the participants in the control group, and they will receive an educational booklet at the end of the study.

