### Data Collection

Eligible patients will be asked to read and sign a written informed consent form. The research nurse will then collect demographic and clinical characteristics by participant self-reporting and from a medical chart and then record these in data collection forms (see Table 1). Also, participants will be asked to complete baseline surveys (SCHFI, HF knowledge, HFQOL, and health literacy) by themselves in the HF clinic before randomization.

In order to assess participant health literacy, we will use the Heart Failure-Specific Health Literacy Scale with Cronbach alpha=.71. It consists of 12 items each with 4 possible scores (1 to 4): inapplicable (1) to strongly applicable (4) where a higher score indicates a higher level of health literacy except items 1 to 4 [55]. The Iranian version of this scale was prepared after getting the developer’s permission. Thus, it was first translated into Persian by a forward-backward translation method. Then, face and content validity were approved by an expert’s opinion (nursing faculty, nurse practitioners, and cardiologists) and discussion with patients with HF. A pilot study was conducted to assess the reliability with 30 HF patients and where a Cronbach alpha value of .77 was determined. Deletion of items could not improve the value similar to the original scale. Therefore, we decided to retain all items [55]. We will ask the participants to complete the health literacy scale as a baseline survey.

In order to measure the HF knowledge at the end of the study, monthly self-care behavior, and the HFQOL, the outcome assessor will be blinded to study group assignments. The assessor will send the DHFKS, SCHFI, and MLHFQ to the participants in both groups by telegram mobile application in the morning of each monthly call follow-up and ask them to send answers before 6 pm of the same day.

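### Exclusion criteria include follow-up events; the diary rule can drop only intervention patients and is expected to tilt the self-care comparison towards the intervention

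*Protocol article*

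**What the plan says.** The eligibility textbox (Methods, Exclusion criteria) lists several events that can happen only once a patient is in the trial:

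- a psychiatric or cognitive diagnosis made during the study;
- sudden "death, migration, or unavailability of patients during the follow-up" phase;
- recording "weight and shortness of breath in the daily diary for less than 60% (<54 days) during the" study;
- undergoing "cardiac or other kinds of surgery with a lengthy hospital stay during the" study.

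Baseline questionnaires are completed "by themselves in the HF clinic before randomization" (Data Collection), so these criteria can act only after allocation.

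The diaries belong to the intervention package. The folder that contains them "will be delivered to each subject in the intervention group" (Methods, Intervention). On the other side, "those in the control group will receive the usual care" (Control), and the Abstract says: "Patients in the control group will receive no intervention and they only complete monthly surveys".

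The primary outcome is the SCHFI self-care score, measured monthly for three months and compared between arms as the mean of the monthly scores (Primary Analysis). Nothing in Statistical Methods overrides the exclusions.

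**The concern.** An exclusion criterion should describe a patient before allocation. One that depends on what happens afterwards breaks up the groups that randomisation formed.

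The diary item is the most serious because it works on one arm. It removes the intervention patients who engage least with self-monitoring and has no counterpart among controls. Daily monitoring is part of the self-care that the package teaches, so patients dropped for poor recording are likely to have lower self-care scores. A package with no effect could then look beneficial on the primary outcome. The Introduction itself notes that "low compliance with weighing has been reported among patients with HF", so the rule may well be triggered.

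The other items are a lesser but real problem. A lengthy surgical stay is itself an admission under the all-cause hospitalization outcome, which counts other cardiac and non-cardiac causes. Excluding such a patient deletes an event from the Kaplan-Meier and log-rank comparison. Excluding patients who die or cannot be reached deletes their time at risk.

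**Working it through.** **1. The plan's own figures.** The weight diary has 6 pages of 15 days and the breathlessness diary 3 pages of 30 days, so 90 days each. 0.60 × 90 = 54, and the cut-off is consistent. The sample size also reproduces. A repeated-measures F test (within-subject or interaction; f = 0.168, 3 measurements, correlation .5, alpha .05, power 80%) needs 60 patients. Then 60/0.90 = 66.7, so 67, or 68 for equal arms. The point below does not depend on an arithmetic error in the plan.

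**2. Inputs.** From Sample Size: SD 27.2, three measurements, correlation .5, 34 per arm, MCID 10. Assumed, because the protocol does not give them: the share q of the intervention arm below 54 days, and the correlation r between diary adherence and the self-care score. The true effect is set to zero.

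**3. SD of the three-month mean.** 27.2 × √((1 + 2 × 0.5)/3) = 27.2 × √(2/3) = 22.2.

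**4. Bias.** If the lowest share q on a normal adherence scale is removed from one arm, that arm's expected mean rises by

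bias = r × 22.2 × k, with k = φ(z)/(1 − q) and z the q-quantile of the standard normal.

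- q = 10%, r = .3: k = .1755/.9 = .195; bias = .3 × 22.2 × .195 = 1.3
- q = 20%, r = .5: k = .2800/.8 = .350; bias = .5 × 22.2 × .350 = 3.9
- q = 30%, r = .7: k = .3477/.7 = .497; bias = .7 × 22.2 × .497 = 7.7

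With a weak link the bias is small: at r = .1 it is 0.4, 0.8 and 1.1 points for q = 10%, 20% and 30%.

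**5. Type I error.** The standard error is 22.2 × √(1/34 + v/n), with n = 34(1 − q) and v = 1 − r²k(k − z) for the reduced variance after selection. The two-sided error is P(Z > 1.96 − bias/SE) + P(Z < −1.96 − bias/SE). Simulation used 6,000 trials per case and a two-sample t test.

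| q, r | v | n | SE | bias/SE | Normal approximation | Simulated |
|---|---|---|---|---|---|---|
| 10%, .3 | .974 | 30.6 | 5.50 | 0.24 | .056 | .060 |
| 20%, .5 | .896 | 27.2 | 5.55 | 0.70 | .108 | .099 |
| 30%, .7 | .751 | 23.8 | 5.48 | 1.41 | .29 | .261 |

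The bias in points is proportional to the SD. The type I error is not affected by it, because bias and SE scale together.

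**6. Against the attrition allowance.** The plan allows 10% of 68 = 6.8 patients. Diary exclusions of 20% of one arm are 0.20 × 34 = 6.8, the whole allowance with no other loss; 30% is 10.2 and exceeds it. With 10% other loss in both arms plus 20% diary exclusion in the intervention arm, 30.6 + 30.6 × 0.8 = 55.1 patients remain, fewer than the 60 in step 1.

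**The case against.** Several counter-arguments have weight.

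- **Analysis sets may be defined elsewhere.** This is a journal article and an analysis plan may exist. The article does not say that excluded patients' data are discarded. That stands, so the absence of an intention-to-treat sentence is not the point. The point is a rule that the article does state. The diaries are handed in at the end of the study, so a criterion based on the total days recorded is settled late and has little use other than to remove patients from the results.
- **The rates are not the plan's.** Calls on days 1, 3 and 7 and weekly after that are meant partly to sustain recording. The remark on poor compliance with weighing gives no rate and does not describe patients receiving such calls. The plan also calls 27.2 the largest SD, so the biases in points lie at the upper end. This stands: the 10% case is as plausible as the larger ones, and its effect is modest.
- **A reader might infer that every listed exclusion favours the intervention.** The protocol does not support that. Death, migration, unavailability, new diagnoses and surgery can occur in either arm, and nothing fixes their balance. A lower overall count of admissions does not imply a difference between arms.
- **A reader might infer that all surgical admissions are removed.** Only surgery with a lengthy stay is named.
- **A reader might take the diary rule to exclude every control,** since controls record on no days. The rule makes sense only for patients who were given a diary.

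**Conclusion.** The concern holds for the diary rule as a directional bias in the primary comparison, and this should be fixed before analysis. The rule acts after randomisation, in one arm, and on a behaviour close to the outcome. The direction rests on one assumption, that diary adherence and the self-care score are positively correlated, which is likely given what the package trains.

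The size is uncertain: from about 1.3 points with almost no inflation of type I error (10% excluded, correlation .3) to about 7.7 points and about .26 (30%, .7), with 3.9 points and about .10 in between. The largest case requires more loss than the plan allows for in total.

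The remaining follow-up exclusions also remove randomised patients for outcome-related reasons, most clearly for hospitalization. Their effect on the difference between arms is unknown.

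**What to change.** - Limit the exclusion criteria to conditions present before randomisation.
- Analyse all randomised patients in their assigned arm, whatever their diary completion, surgery or later diagnosis, using every monthly score collected.
- For the questionnaire outcomes, treat death, migration and unavailability as missing data, not as exclusions.
- For hospitalization, keep these patients at risk until death or last contact, count lengthy surgical admissions as events, and report deaths by arm. The endpoint itself stays hospitalization.
- Report diary completion (at least 54 of 90 days) descriptively for the intervention arm, and label any adherer-only analysis as a sensitivity analysis.

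The cost is wording plus continued monthly contact with a few patients. The monthly questionnaires and hospitalization calls already run in both arms and do not need the diary. The article's dates leave open whether follow-up has ended. If it has, the change can still be made at analysis for data already collected, with scores not collected after an exclusion handled as missing. The downside is that the estimated effect may be smaller.

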**Figure 1 figure1:**
[figure not shown]
Colored weight daily diary. EMS: emergency medical services.

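### The weight-diary zone lines appear to be set from a clinic-scale weight but are read against home-scale weights, so any constant offset between the two scales shifts both zones

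*Protocol article*

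**What the plan says.** All of this is in the protocol article; the diary text is in the Intervention section.

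- **Clinic weight.** At referral, "the HF specialist will measure the weight of eligible participants by analog weight scale"; a single clinic model is named.
- **Zone lines.** The next sentence opens with 'Then' and says that "2 upper control limits will be determined for participants by the research nurse to identify 1 and 2.5 kg greater than the baseline weight". These are the yellow and red zones of the weight diary, and they carry no time window.
- **Home weights.** Textbox 1 requires each patient to own a working scale, digital or analog. Patients weigh themselves on it daily, before breakfast and after using the toilet, in similar clothing and at a fixed hour. No such conditions are given for the clinic weight, and no cross-check of the two scales is described.
- **Rate rule.** Patients are also told to contact the research nurse for "sudden weight gain of 1 kg in one day (yellow zone) and 2.5 kg in one week (red zone".
- **Action sentence.** The shortness-of-breath (SOB) paragraph ends by telling patients to "contact the research nurse if they reach the yellow color zone to increase the diuretic dosage" and to make "contact with the emergency medical services in the red color zone".
- **Calls.** The nurse telephones on days 1, 3 and 7 and then weekly, in the evening, and asks which colour zone the patient has been in.

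**The concern.** A line at baseline plus 1 kg means what it says only if the baseline and the plotted weights are on the same footing. Here they appear to come from two instruments, and the weighing conditions are standardised for only one of them. The yellow margin is just 1 kg, so even a modest offset is large beside it.

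The weight zones are the intervention's prompt to act on fluid retention. If home reads high, patients enter yellow without having gained weight; this would probably come to light at the early calls. If home reads low, yellow and red come late. That is the less visible direction, because the nurse asks about the colour zone and the patient would still report green.

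A second, smaller matter is that the same colour labels are attached both to a level above baseline and to a rate of gain, and the text shown does not say how the two combine.

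**Working it through.** There is no calculated figure in the plan to reproduce; its own inputs are the two thresholds.

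**Inputs from the protocol article:** level limits of 1 kg (yellow) and 2.5 kg (red) above baseline; rate limits of 1 kg in a day (yellow) and 2.5 kg in a week (red).

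**Assumed, not in the documents:** a constant offset d = home reading minus clinic reading, from -1 to +1 kg; a steady true gain of 0.3 kg/day from baseline.

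**Level lines.** The plotted reading on a given day is clinic baseline + d + true gain. The line at baseline + L is reached when true gain = L - d. So yellow needs 1 - d and red needs 2.5 - d. The day of crossing is that gain divided by 0.3, rounded up to a whole day.

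| d (kg) | Gain for yellow | Gain for red | Yellow day | Red day |
|---|---|---|---|---|
| -1 | 2.0 | 3.5 | 7 | 12 |
| -0.5 | 1.5 | 3.0 | 5 | 10 |
| 0 | 1.0 | 2.5 | 4 | 9 |
| +0.5 | 0.5 | 2.0 | 2 | 7 |
| +1 | 0 | 1.5 | 0 | 5 |

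For example, at d = -1, 2.0/0.3 = 6.67, so day 7, and 3.5/0.3 = 11.67, so day 12. Compared with no offset, both zones come three days late. At d = +1 a patient with no gain is already on the yellow line.

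**Rate rule.** The difference between two readings on the same scale is (gain₂ + d) - (gain₁ + d) = gain₂ - gain₁. The offset cancels, so this rule is unaffected.

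**Secondary point: level and rate can label the same patient differently.**

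- At 0.3 kg/day with no offset, day 9 is 9 × 0.3 = 2.7 kg, red by the line. The weekly gain is 7 × 0.3 = 2.1 kg, below 2.5, so there is no zone by rate. Any steady gain below 2.5/7 = 0.357 kg/day never meets the rate rule.
- A patient who starts 1 kg below baseline and gains 2.5 kg in a week stands at +1.5 kg: yellow by the line, red by rate.

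**The case against.** **On the scale mismatch.** The text does not expressly call the clinic reading the baseline weight; 'Then' implies it. The size and direction of any offset are undocumented, and the gain path is a noise-free assumption. It is tempting to infer that clinic weights run high because patients are clothed or have eaten, but the article does not state the clinic conditions. The rate rule, daily SOB scoring, the scheduled calls and the HF specialist all limit the harm. All of this stands, and it holds the point to a minor one. It does not remove it, because nothing in the text puts the lines and the plotted weights on one scale.

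**On the two zone definitions.** A reader might infer that the protocol contradicts itself, either leaving slow gain with no patient call or sending red weight gain to both the nurse and emergency services. The documents do not support that.

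- The words 'also' and 'sudden' in the rate sentence read naturally as an acute alert added to the plotted lines.
- The two harms need opposite readings of one sentence. If the closing action sentence covers SOB only, weight has one destination, the nurse, and slow gain waits at most for the next scheduled call. If it covers both diaries, slow gain does prompt a call, and only then does red weight gain have two destinations.
- Figure 1, whose caption reads "Colored weight daily diary. EMS: emergency medical services", Figure 3 (nurse actions by zone) and the diary's instruction page could settle both questions. None of them is shown.

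What remains is a request for clarity, not a demonstrated error.

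**Conclusion.** The scale mismatch holds on the text, on the plain reading of 'Then'. Following the plan as written, any constant home-minus-clinic offset shifts both lines by its full amount. At an assumed -1 kg the true gain needed for yellow doubles, from 1 to 2 kg, and that for red rises from 2.5 to 3.5 kg; at +1 kg a stable patient starts on the yellow line. The arithmetic is exact, but the offset range and the 0.3 kg/day path are illustrations.

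This is a minor safety and fidelity improvement. Sample size, alpha and the SCHFI analysis are not affected. How the level and rate rules combine, and what a patient does on red weight gain, is a low-priority clarification that the figures not shown may already settle.

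**What to change.** **Main change.** Set the yellow and red lines from the first standardised morning reading on the patient's own scale, reported at the existing day-1 call (day 3 if missed). Until then the clinic-scale lines are provisional and drawn in pencil; the patient's folder already holds a pencil and eraser. The 1 and 2.5 kg limits stay as they are. Day 1 is better than day 3 because drug doses may be adjusted at enrolment (Participant Recruitment), which could itself move weight.

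**Secondary, low priority.** State in the Intervention text and on the diary's first page that meeting either the baseline limit or the rate rule prompts contact, and that the higher zone applies, subject to the HF specialist's agreement. Give one action for red weight gain, the same in the text and in Figures 1 and 3. If the figures already fix this, bring the text into line with them.

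**Cost.** The main change adds one recorded value at an existing call and a short change to the diary instruction and nurse script. Lines redrawn by telephone carry some risk of transcription error: 2 lines on up to 6 recording pages, so up to 12, if each page carries them. The either-rule wording may bring a few more patient calls. If emergency services is the action chosen for red, slow non-fluid gain to +2.5 kg would go there too, which the HF specialist should weigh. Enrolment had begun at submission (Results), so the change goes to the IRB and REC, and patients enrolled before and after it will differ slightly in how their lines were set.
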